#### Secondary outcomes

Body Mass Index (BMI) and waist circumference will be registered at the beginning, midpoint, and end of each intervention period by qualified staff. Systolic and diastolic blood pressures will be determined three times at 5-min intervals while volunteers are seated using a standardized mercury sphygmomanometer; the final two measurements will be averaged for the analysis.

Serum glucose, insulin, Homeostasis Model Assessment (HOMA) index, cholesterol, LDL, HDL, triacylglycerols, glutamate-pyruvate transaminase (GPT), glutamate-oxaloacetate transaminase (GOT), gamma-glutamyltransferase (γ-GT), glycated haemoglobin, and C-reactive protein will be determined before and at the end of each intervention period by standard methods.

Inflammatory and CDV biomarkers, including adiponectin, resistin, myeloperoxidase (MPO), plasminogen activator inhibitor-1 (PAI-1), tumour necrosis factor-alpha (TNF-α), interleukin-6 (IL-6), interleukin-8 (IL-8), soluble intercellular adhesion molecule-1 (sICAM-1) and soluble vascular adhesion molecule-1 (sVCAM-1), will be measured using MILLIPLEXMAP test kits (Milliplex Map Kit, Millipore Corp, Billerica, MA). Arginase, prolidase and retinol binding protein-4 will be measured as hepatic steatosis markers. The arginase and prolidase activity will be measured according to Palomero-Rodriguez et al. [17] and Kayadibi et al. [18], respectively, whereas RBP-4 will be determined by ELISA technology (AdipoGen Inc).

For the study of intestinal microbiota composition, a 16S metagenomics sequencing will be performed. In brief, faecal DNA will be extracted using a commercial isolation kit (QIAamp DNA Stool Mimi Kit, Qiagen). The variable V3 and V4 regions of the 16S rRNA gene will be PCR-amplified and sequenced on an Illumina MiSeq platform at Hospital Universitario San Cecilio, Spain, following the Illumina recommendations.

### Withdrawal, dropout, discontinuation, and compliance

Withdrawal will be allowed at any time during the trial. Participants may be advised to discontinue the trial if there is no compliance or if a severe adverse event occurs. Women will be advised not to become pregnant during the study. Participants will be instructed to return the unconsumed capsules when collecting the follow-up doses. Participants whose compliance with treatments or placebo is ≤80% of the total, those who become pregnant and those who develop diabetes will be considered dropouts.

### Adverse events and safety monitoring

All *Lactobacillus* strains are considered safe by the EFSA (European Food Safety Authority). However, each participant will be monitored for abdominal discomfort, diarrhoea, bloating, constipation and nausea/vomiting, among other possible effects, during each visit, and all unexpected adverse events will be reported by participants and written on the individual case report form by the investigator.

### Sample size and power analysis

Based on the range and median value of LPS [8] and assuming a power of 80% and a significance level of 5%, the minimum number of subjects will be 21 per arm. To avoid possible bias caused by gender and taking into account withdrawal, we will be recruiting a total of 60 subjects. Missing data will be considered as unavailable data.

### Statistical analysis

Data analyses will be performed at the end of the intervention, therefore, a replacement or substitution of a withdrawal subject is not planned; therefore, the missing data will be considered unavailable data.

The normality of variables will be assessed. Variables not following a normal distribution will be transformed. Normal variables will be expressed as the mean and standard error of the mean. An intention-to-treat analysis will be performed for the analysis of efficacy. In order to determine differences in basal characteristics, a paired *t-test* will be used. Carryover effects will be assessed by three-way ANOVA. A general lineal model for repeated measurements will be performed to evaluate differences between variables at the beginning, midpoint, and end of each intervention period. Two-way ANOVA will be used to determine the influence of treatment (probiotic or placebo) and time on the continuous dependent variables. Statistical analyses will be performed using IBM SPSS statistics v22.

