**Methods/design:**

We describe a randomized, double-blind, crossover, placebo-controlled, and single-centre trial. Sixty participants (aged 18 to 65 years) diagnosed with IRS will be randomized in a 1:1 ratio to receive either a daily dose of placebo or 5 × 10^9^ colony-forming units of *L. reuteri* V3401. The study will consist of two intervention periods of 12 weeks separated by a washout period of 6 weeks and preceded by another washout period of 2 weeks. The primary outcome will be the change in plasma lipopolysaccharide (LPS) levels at 12 weeks. Secondary outcomes will include anthropometric parameters, lipid profile, glucose metabolism, microbiota composition, hepatic steatosis, and inflammatory and cardiovascular biomarkers. Blood and stool samples will be collected at baseline, at the midpoint (only stool samples) and immediately after each intervention period. Luminex technology will be used to measure interleukins. For statistical analysis, a mixed ANOVA model will be employed to calculate changes in the outcome variables.

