### Randomization, allocation, and blinding

Patients will be randomly allocated in a 1:1 ratio to receive a capsule containing either lyophilized *L. reuteri* V3401 or placebo once daily with food for 12 weeks. A stratified block-randomization method of a software program for sequence generation will be used. After a 6-week washout, participants will crossover to receive the alternative intervention for another 12 weeks. Subjects and investigators will be blinded to the treatment allocation during the course of the intervention. The blind will be broken following consultation with the sponsor.

The capsules will be prepared in special containers with the random number label. Capsules will be delivered at the beginning of each intervention and six weeks later to ensure probiotic viability.

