### Dietary and physical activity control

Participants will be provided with a list of local foods to avoid due to their potential probiotic or prebiotic content. Subjects will be asked to complete a three-day dietary record at the beginning, midpoint, and end of each intervention period. Energy and dietary intakes will be assessed from the 3-day records using the EvalFINUT software (http://www.finut.org/evalfinut/). Additionally, subjects will complete the Food Frequency Questionnaire (FFQ) at the beginning of each intervention period. Participants will receive nutritional counselling on a healthy Mediterranean diet providing approximately 25 kcal/kg/ day to achieve and maintain 7% loss of initial body weight and increase moderate-intensity physical activity (such as brisk walking) for at least 150 min/week following the guidelines of the American Diabetes Association for the prevention or delay of DM2 [15]. Likewise, physical activity will be monitored through the International Physical Activity Questionnaire (IPAQ) at the beginning, midpoint, and end of each intervention period. In the following visits, an intensive lifestyle intervention programme will be carried out to reinforce the behaviour.

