### Outcome measures

Clinical and anthropometric parameters (weight, height, waist circumference and blood pressure) will be recorded. A hepatic ultrasound (US) test will also be performed at the beginning of the two intervention periods, as well as at the end of the intervention periods. US diagnostic criteria for diagnosis and grading of hepatic steatosis will be used [16]. Smoking habits and anxiolytic and antihistaminic drug intake will also be recorded.

Blood samples will be collected after 12 h of fasting at the beginning and at the end of each intervention period (t0, t12, t18 and t30). Stool samples will also be taken at baseline and at 6, 12, 18, 24, and 30 weeks (t0, t6, t12, t18, t24, and t30, respectively). Serum will be collected by centrifugation of blood samples for the determination of biochemical and inflammation biomarkers. Faecal samples will be collected and kept at − 80 °C until analysis. All samples will remain frozen at − 80 °C in the BSSPA Platform.

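### No efficacy model named for this AB/BA crossover states a period term, and the protocol does not say which of its models gives the primary LPS result

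*Protocol article*

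**What the plan says.** The design is a two-period crossover. "Patients will be randomly allocated in a 1:1 ratio to receive a capsule" of probiotic or placebo, and "After a 6-week washout, participants will crossover to receive the alternative intervention for another 12 weeks" (Randomization, allocation, and blinding). The primary outcome is the change in plasma LPS (Primary outcome).

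The protocol article names four analyses of the outcomes:

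- **Two-way ANOVA** (Statistical analysis): "Two-way ANOVA will be used to determine the influence of treatment (probiotic or placebo) and time on the continuous dependent variables". This is the only sentence that ties a model to the treatment effect.
- **Repeated-measures model** (Statistical analysis): "A general lineal model for repeated measurements will be performed to evaluate differences between variables at the beginning, midpoint, and end of each intervention period".
- **Three-way ANOVA** (Statistical analysis): assigned to carryover, with its three factors not named.
- **Mixed ANOVA** (Abstract, Methods/design): "a mixed ANOVA model will be employed to calculate changes in the outcome variables".

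Blood is drawn "at the beginning and at the end of each intervention period (t0, t12, t18 and t30"), so LPS has no midpoint value; Table 1 agrees. The dietary section sets a programme "to achieve and maintain 7% loss of initial body weight" and to raise physical activity, reinforced at later visits. The Intervention section adds that no dietary recommendations are given in the washout.

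**The concern.** In an AB/BA crossover each person supplies one period on each treatment, so anything that makes period 2 differ from period 1 is mixed into the within-person treatment difference unless the model has a period term.

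Here such a difference is plausible on the protocol's own account. The lifestyle programme is aimed at a lasting weight loss and is reinforced as the trial proceeds, so participants do not enter the second period in the state in which they entered the first. The Discussion itself describes diet as a main influence on the gut microbiota and LPS as a product of gut bacteria.

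At stake are the precision of the primary comparison and, if withdrawals fall unevenly on the two sequences, its freedom from bias. There is also a simpler problem: with several model names and no designation, a reader cannot tell which analysis will give the LPS result.

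**Working it through.** **1. The plan's own figure.** The sample-size section gives 21 per arm at 80% power and 5% significance, but no effect size or SD, so it can be neither confirmed nor refuted. Under a two-sided parallel-group formula, 21 per arm corresponds to a standardised difference of (1.960 + 0.842) × √(2/21) = 0.865. Nothing below depends on this. I use 2 × 21 = 42 completers as the working number.

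**2. Which models carry period?**

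| Model | Stated factors | Period stated? | Role |
|---|---|---|---|
| Two-way ANOVA | treatment, time | No; time undefined | treatment effect |
| Repeated-measures model | beginning, midpoint, end of each period | No | change over time |
| Mixed ANOVA (abstract) | none given | No | change in outcomes |
| Three-way ANOVA | none given | Unknown | carryover |

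**3. Effect of leaving period out, subject retained.** Let τ be the treatment effect, π the period-2 minus period-1 shift in LPS change, and D the within-person probiotic-minus-placebo difference in change, with variance v. Then:

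- probiotic first (n_AB people): mean of D = τ − π
- placebo first (n_BA people): mean of D = τ + π

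The paired analysis averages D over everyone, so

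- estimate = τ + π × (n_BA − n_AB)/N
- with equal sequences, the variance used by the test is about v + π², although the true sampling variance of the mean is still v/N. The standard error is too large by √(1 + π²/v).

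**4. Size with 21 + 21 completers.** Assumptions, none of them from the protocol: four LPS readings per person, each with SD 1 and equal correlation ρ; π in units of that SD; τ set to give 80% power with period in the model. Then v = 4(1 − ρ). On 40 degrees of freedom, 80% power needs τ/SE = 2.871; the paired test on 41 degrees of freedom has critical value 2.020. Power without period ≈ Φ(2.871 − 2.020 × √(1 + π²/v)).

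| ρ | v | SE ratio, π = 0.5 | Power | SE ratio, π = 1 | Power |
|---|---|---|---|---|---|
| 0.3 | 2.8 | 1.044 | 78% | 1.165 | 70% |
| 0.5 | 2.0 | 1.061 | 77% | 1.225 | 65% |
| 0.7 | 1.2 | 1.099 | 74% | 1.354 | 55% |

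Two simulations of the 1 SD case gave 70/67/55% and 69/65/54%. Type I error there was 2.4/1.5/0.7% against a nominal 5%, so the test is conservative.

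**5. A second parametrisation.** Here the change score has SD 1, ρ is the correlation between the two period changes (0.3 to 0.7), and the true effect is 0.5 SD. With equal sequences, power without and with period was 0.71–0.96 against 0.76–0.98 at a 0.5 SD shift, and 0.53–0.80 against 0.76–0.98 at 1 SD. The loss has the same direction and again grows with the shift.

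**6. Unequal sequences.** With 24 probiotic-first and 18 placebo-first completers, the bias is π × (18 − 24)/42 = −0.143π, that is 14% of the shift. With 27 and 15 it is −12/42 = −29%. In the second parametrisation with a 1 SD shift and 24 against 18, a true effect of 0.50 was estimated at about 0.36, and power was 0.26–0.40 against 0.76–0.99 with period in the model. Reversing the imbalance or the sign of the shift exaggerates the effect instead.

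**The case against.** The strongest defence is that this is a condensed article. Full model terms normally stand in the full protocol or analysis plan, and the article nowhere says that period will be excluded. Time is not defined; if it means the calendar visit (weeks 0, 12, 18, 30), it carries at least part of the period effect. Sequence could be one of the unnamed factors in the carryover ANOVA. Allocation is 1:1 in stratified blocks, so bias needs uneven dropout. The 1 SD shift and the 24/18 split are assumptions.

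Most of this limits the size of the point. It does not remove it, because the article does state a model for the treatment effect, and its two factors do not suit the design unless time is read generously. A carryover test does not supply the treatment estimate. Uneven dropout is possible: withdrawn participants are not replaced, missing values are left unavailable, and compliance of 80% or less counts as dropout.

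Two stronger readings should be resisted:

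- **That subject is left out altogether.** Two-way counts factors, and subject as error stratum is not usually counted. The repeated-measures and mixed labels both imply within-person structure. If all readings were nevertheless treated as independent, the loss would be larger (simulated power about 70/53/25% at ρ = 0.3/0.5/0.7 with no period shift), but the text does not establish that reading.
- **That the repeated-measures model cannot be fitted to LPS.** It can, with two time points per period. The sentence is loosely worded for an outcome without a midpoint.

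**Conclusion.** The point holds in a limited form. No efficacy model named in the article states a period term, no model is designated for the primary LPS comparison, and the abstract and the methods section use different names. A period effect is plausible because of the lifestyle programme, although the protocol gives no information on its size, and the absence of dietary recommendations in the washout could move it either way.

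If period is in fact omitted, the main harm with equal sequences is lost precision: a few percentage points of power at a 0.5 SD shift, and about 10 to 25 points at 1 SD. A reader might infer a biased treatment effect from the outset; that does not follow under 1:1 sequences. Bias appears only when completers are unequal across sequences, in proportion to the imbalance. All power figures rest on assumed correlations, shifts and 42 completers; the bias formula for an analysis without period does not depend on those values.

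**What to change.** Name one primary model for LPS: the within-period change (week 0 to 12, week 18 to 30), with treatment, period and sequence as fixed effects and subject as random. It uses the period baselines already collected. Transform LPS if it is not normal, as the plan already provides. Report the probiotic-minus-placebo difference with its 95% confidence interval.

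Say what time means wherever it is used as a factor. Apply the beginning/midpoint/end model only to outcomes that have a midpoint value (blood pressure, anthropometry, stool). Use the same model name in the abstract and the methods section, and date the change before the blind is broken.

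The cost is one rewritten paragraph and one or two degrees of freedom (for example 40 instead of 41 for the within-person comparison with 42 completers). No new data are needed, and the planned software, SPSS v22, can fit the model.

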## Discussion

The present study has been designed to demonstrate whether a probiotic strain, *L. reuteri* V3401, is capable of reducing the IRS components together with healthy lifestyle recommendations (hypocaloric diet and physical activity).

Currently, altered intestinal microbiota is considered a new player in IRS based on its capacity to promote a state of low-grade systemic inflammation, insulin resistance and increased cardiovascular risk through mechanisms that include exposure to bacterial products such as LPS, a component of the outer membrane of gram-negative bacteria. It is currently accepted that the increase in serum levels of LPS produces a metabolic endotoxaemia capable of modulating pro-inflammatory cytokines, as well as glucose and lipid metabolism in the liver and adipose tissue. There is scientific evidence to support the contribution of LPS in DM2 and obesity [7]. Additionally, on the basis of studies in both animals and humans, dietary intake appears to be a major regulator of the structure and function of the gut microbiota [19]. Therefore, promoting changes in the gut microbiota combined with an adequate Mediterranean diet might play an important role in ensuring the efficacy and success of reducing IRS components and avoiding DM2 development.

However, a relatively small number of randomized, clinically controlled studies assessing the beneficial effects of probiotics on metabolic syndrome parameters have been reported. When looking for a specific clinical response, special care must be taken when selecting the strain because probiotic effects are strain specific [12]. The effects of probiotics are explained by their contribution to the intestinal microbiota composition, maintenance of gut barrier function and their immunomodulation capacity [10, 12].

As mentioned above, the most commonly used strains of probiotics are *Bifidobacterium* and *Lactobacillus* spp*.* The consumption of *L. acidophilus* NCFM has been described to preserve insulin sensitivity without affecting systemic inflammation [20]. Furthermore, *L. reuteri* LR6 has been shown to decrease total cholesterol values and increase HDL-cholesterol levels in the plasma of rats fed a hypercholesterolemic diet [21]. In humans, enrichment of gut microbiota with *L. reuteri* SD5865 has been reported to increase insulin secretion, possibly due to augmented incretin release, although this strain does not seem to affect insulin sensitivity or body fat distribution [22]. However, in a correlation study, Million et al. detected *L. reuteri* in 20% of their study population, with occurrence increasing along with BMI values (7, 8, 34 and 22% for anorexic, lean, overweight and obese individuals, respectively) [23].

To the best of our knowledge, no studies have tested the possible beneficial effect of *L. reuteri* V3401 in patients with IRS. Based on the background provided above, we propose to study the *L. reuteri* V3401 strain by means of an intervention study in subjects with IRS who will follow a healthy lifestyle (hypocaloric diet and physical activity).

## Abbreviations

BMI: Body Mass Index
Cfu: Colony forming units
CVD: Cardiovascular disease
DM2: Diabetes mellitus 2
EFSA: European Food Safety Authority
FFQ: Food Frequency Questionnaire
GOT: Glutamate-oxalacetate transaminase
GPT: Glutamate-pyruvate transaminase
HDL: Serum high-density lipoprotein
HOMA: Homeostasis Model Assessment
IDF: International Diabetes Federation
IL-6: Interleukin-6
IL-8: Interleukin-8
IPAQ: International Physical Activity Questionnaire
IRS: Insulin resistance syndrome
LBP: Serum LPS binding protein
LPS: Lipopolysaccharide
MPO: Myeloperoxidase
NAFLD: Non-alcoholic fatty liver disease
PAI-1: Plasminogen activator inhibitor-1
sICAM-1: Soluble intracellular adhesion molecule-1
sVCAM-1: Vascular adhesion molecule-1
TNF-α: Tumor necrosis factor-alpha
US: Ultrasound
γ-GT: Gamma-glutamyltransferase
